### Monitoring

#### Data Monitoring Committee (DMC)

The DMC, chaired by [name] ([contact]), will meet regularly (as required) to assess trial progress based on independent trial data (e.g., actual recruitment to trial against projected trial recruitment), provided by the Robertson Centre for Biostatistics CTU and will be given the power to stop the trial should the committee see fit.

If analysis of follow-up data shows that maternal psychological distress significantly worsens after participation in either intervention, we shall seek guidance from the Trial Steering Committee (TSC) and DMC about how to respond, as by that time all of the participants allocated to the ETPB and MB arms will have already received an intervention.

#### Trial Steering Committee

THRIVE will be supported by a TSC comprising academic and health professionals, all of whom are specialists in early years and/or maternal mental health. The TSC will also have a lay member. The committee will be chaired by [name], Plymouth University ([contact]). It will meet once or twice a year (as required) to provide advice to the research team. Exceptional meetings can be called by the Chair or the Chief Investigator (CI) if guidance is sought as a matter of urgency. Publication plans will be discussed in full with the TSC.

#### Potential harms

*Data collection*

THRIVE will adhere to Good Clinical Practice guidelines on safety reporting in clinical trials. Our quantitative data collection procedure will consist of completing repeat questionnaires with trained researchers (including Good Clinical Practice training), all of whom will have undergone criminal background checks and have significant experience of working with vulnerable groups. Whilst the questionnaire consists of well-established measures that are not known to be problematic, it is possible that participants may become upset whilst completing the questionnaires. All researchers will receive training in how to handle participant distress and will follow NHS guidance relating to patient confidentiality and protection, including vulnerable adult and child protection procedures. A “useful contacts” sheet will be given to all participants to signpost them to relevant service providers.

Should a researcher become concerned about a participant, s/he will raise this concern with relevant health and/or social care professionals to ensure the participant receives the adequate care they require. In this situation, researchers will complete an incident report form outlining the steps taken and a decision will be made by the CI, Project Manager (PM) and Sponsor as to whether the incident should be reported as an adverse event. The same risks are present in conducting qualitative interviews with participants. All interviewers will have experience in conducting qualitative interviews and working with vulnerable populations and will follow the aforementioned procedures if participant distress is evident.

While researchers may signpost participants to further support services, or, with the participant’s consent, contact their health or social care providers to initiate ongoing support, no formal ongoing post-trial support will be offered by the research team themselves.
b)
*Participation in the interventions*

We will be working with vulnerable women at a sensitive period in their lives, and some activities, such as being asked to reflect upon past experiences, may have the potential to cause distress: however, other research suggests asking about adverse childhood events does not cause measurable distress [61]. Furthermore, we believe that this risk is minimal because both interventions are designed to reduce stress through positive action and the development of coping strategies. In addition, the group facilitators will undergo training to work with this group of women and will be able to provide empathetic support and signpost participants to services should they require additional support. The group dynamics may help to reduce stress/distress to participants by providing a supportive and considerate atmosphere in which issues can be discussed. However, it must be recognised that the delivery of ETPB and MB within group settings carries a risk that participants might choose to discuss issues raised with others outside of the group setting. As the focus of the group sessions is more on activities and active discussion rather than disclosing personal histories, the risk of this occurring is low. Nevertheless, to promote respect and confidentiality amongst participants the intervention facilitators will work with them to establish group rules about confidentiality, especially in relation to social media. Furthermore, the bringing together of vulnerable participants may result in the formation of positive or negative group interactions and social networks. Group facilitators will be given the adequate support and resources necessary to signpost participants to appropriate services. At all times, groups facilitators will adhere to NHS guidance relating to patient confidentiality and protection, including vulnerable adult and child protection procedures, and report any concerns about participants to both the PM and their line manager at the NHS GGC Clinical Research Facility; the CI will also be kept informed and be able to influence decision-making.

Should a participant have any concerns about their participation in THRIVE they will be advised to contact the trial PM, CI or the University of Glasgow, Institute of Health and Wellbeing Research Support Manager. These contact details will be included in the trial information booklet given to each participant before they consent to participate in the trial.

*Withdrawal from the interventions or trial*

Participants may choose to withdraw from the intervention group or the trial at any point. Participants will be asked a reason for withdrawal, but will not be required to respond. Participants who withdraw from the intervention but not the trial will still be eligible for follow-up data collection.

Any women that report experiencing harm from attending the group will be given the support discussed previously and advised by the research team to stop attending the groups. Participants may also be advised by their health or social care practitioner to stop attending groups or withdraw from the trial, based on ongoing health or social care needs. Any participant found to be inflicting harm on another participant or group facilitator will be asked to leave the group sessions and will be withdrawn from further data collection.

It will not be appropriate for participants who no longer meet the study eligibility criteria due to intrauterine death or stillbirth to be invited to subsequent group sessions, and no further intervention or follow-up assessment will be offered to these participants. Women who give birth prematurely while the antenatal sessions of each intervention are ongoing will no longer be eligible to attend antenatal elements of the group but will be offered the postnatal sessions.

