#### Care-as-usual (CAU)

All participants in this study will continue to receive their routine antenatal and postnatal care. Generally, this involves care from hospital and community-based healthcare specialists, such as midwives, obstetricians and health visitors. The exact care received by each participant will depend on their individual additional health and social care needs and may also engage services from other sources including social work services and voluntary agencies. All care received will be in line with local authority and Government policy and guidelines [19, 26–30]. The specific services accessed by each participant as part of their CAU will be captured in service use diaries.

Participants randomised to the CAU arm of the trial will not be offered either intervention (ETPB or MB) in THRIVE on completion of data collection. However, participants may access Triple P International and Mellow Parenting programs as part of their CAU, where these are offered through social work or third-sector organisations within NHS GGC and NHS A&A. Uptake of other parenting programmes outside of THRIVE will be captured in the service use diary.

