#### Baseline: 12–24 weeks pregnant

The baseline questionnaire (Additional file 2) will include the following validated measures:
The Brief Symptom Inventory (BSI-53; Question (Q)48 (Additional file 2)), which is a 53-item questionnaire covering nine symptom dimensions: somatization, obsession-compulsion, interpersonal sensitivity, depression, anxiety, hostility, phobic anxiety, paranoid ideation and psychoticism [31, 32]. The Global Severity Index from this scale will be used in randomisation to indicate severity of symptoms.The Hospital Anxiety and Depression Scale (HADS), which is a 14-item questionnaire assessing symptoms of anxiety and depression [33]. This will be enhanced by the 4-item outwardly directed irritability (I) questions adopted from the Adult Wellbeing Scale (AWS) [34], as a baseline measure for the primary outcome of maternal mental wellbeing (Q47).The EuroQol 5 Dimensions (EQ-5D-3 L; Q49), which is a standardized instrument to measure health-related quality of life, which will be used for health economic analyses [35].The 23-item Recent Life Events questionnaire (Q45), to determine the experience of specific events in the past year, and whether these affect the respondent [36, 37].The 12-item attitudes and pregnancy to the baby subscale from the Maternal Attitudes and Maternal Adjustment questionnaire (Q32) [38].The 28-item Childhood Trauma Questionnaire (Q89) as a measure of childhood abuse and neglect [39].

The baseline questionnaire will also include questions assessing reasons for vulnerability in pregnancy; socio-demographic characteristics including age, Scottish Index of Multiple Deprivation, ethnicity, education and employment; previous childbirth history and parity; health in pregnancy; and substance abuse [40].

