#### Follow up at 6 months postnatal (primary outcome end point)

The primary outcome of maternal mental wellbeing will be assessed by the HADS+I, included in the follow-up questionnaire (Additional file 3; Q35). The primary outcome of mother-infant interaction quality (MIIQ) will be measured based on the CARE Index Dyadic Synchrony Score [41] determined from an episode of play recorded during the follow-up visit when the infant is around 6 months old.

In addition to the HADS+I, the follow-up questionnaire will include the following listed validated measures that will be analysed as secondary outcome measures:

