### Statistical analysis

THRIVE has been powered based on the primary outcome measure of maternal mental wellbeing. The efficacy of ETPB and MB will be analysed at a significance level of 2.5% in order to maintain an overall type I error rate of 5%. Two analyses, performed in a hierarchical fashion so that no further *p* value adjustment is necessary, will be undertaken. In analysis 1, the combined intervention groups (ETPB and MB) will be compared with CAU. If analysis 1 detects a difference at a 2.5% level of statistical significance, analysis 2 will compare ETPB with MB as a primary analysis, to be judged at a 2.5% statistical significance level. If analysis 1 does not yield a statistically significant result, then analysis 2 will be considered a secondary analysis.

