#### Planned analysis

Baseline-adjusted linear regression analysis (analysis of covariance) will be used to compare primary statistical outcomes between intervention groups. Similar methods will be used for other outcomes (using data transformation and alternative regression methods, depending on the distribution of each outcome). Regression models will be extended to investigate the effects of baseline characteristics and the potential moderating effects of these variables and other measures of intervention compliance. Repeated measures methods will be applied to outcomes collected at more than one post-baseline assessment.

For participants discontinuing from the study before the postnatal follow-up data collection, baseline data will continue to be analysed when consent is provided. Missing values will not be imputed. The sensitivity of the primary outcome analysis to missing values will be explored using multiple imputation, generating 10 imputed data sets, using all available data to predict missing values. Analyses will be conducted for the intention-to-treat population, consisting of all participants who have been randomised to the trial. In addition, analyses will also be undertaken for the per-protocol/on-treatment population.

For the economic analysis the incremental costs and benefits in each treatment arm will be reported within an incremental cost-effectiveness ratio (ICER) if appropriate. Within-trial analysis of costs and effects will be undertaken in STATA (StataCorp, TX, USA), adhering to good practice for economic evaluations alongside clinical trials [58, 59]. Missing data will be explored by employing multiple imputation methods using alternative configurations of baseline covariates [53, 60]. Based on the availability of linked routine data, longer-term costs and outcomes will be assessed by linking short-term outcomes identified in the study to potential longer-term impacts on health and wellbeing for both mother and infant, via trial extrapolation methods including economic modelling techniques.

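### Women removed from a group for harming others also lose their outcome follow-up, a loss that can occur only in the two intervention arms

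*Protocol article*

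**What the plan says.** The rule is in the protocol article, Potential harms, in the part on withdrawal from the interventions or trial. It is triggered by "Any participant found to be inflicting harm on another participant or group facilitator", and such a woman "will be asked to leave the group sessions and will be withdrawn from further data collection". The rule is unconditional and is applied by the trial, not chosen by the woman.

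A paragraph earlier, the same section treats other leavers differently: "Participants who withdraw from the intervention but not the trial will still be eligible for follow-up data collection".

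Three further places bear on this:

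- Care-as-usual (CAU): "Participants randomised to the CAU arm of the trial will not be offered either intervention (ETPB or MB) in THRIVE".
- Statistical analysis: in analysis 1, "the combined intervention groups (ETPB and MB) will be compared with CAU".
- Planned analysis: "Analyses will be conducted for the intention-to-treat population, consisting of all participants who have been randomised to the trial". Missing values are left unimputed in the main analysis. Multiple imputation with 10 data sets is a sensitivity analysis for the primary outcome.

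On the outcome itself, the follow-up section says: "The primary outcome of maternal mental wellbeing will be assessed by the HADS+I". The baseline section explains that the added I stands for four items on outwardly directed irritability.

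**The concern.** The clause ties two separate decisions together: whether a woman may stay in the groups, and whether her outcome is collected. The first is a matter for the sponsor. The second decides which randomised women contribute to the primary comparison.

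The trigger is behaviour in a setting that CAU women do not enter within the trial, so the loss depends on arm. It may also depend on outcome, since harming others lies close to outwardly directed irritability. Analysis 1 is affected directly, and it also determines whether analysis 2 counts as primary.

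The planned analyses do not repair this. The main analysis uses observed scores. Multiple imputation predicts from women who have scores, and the rule means that removed women normally have none, so the data cannot show how far they differ from women with similar baseline values.

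**Working it through.** **The plan's own figures.** The point rests on no figure in the article, but the design numbers set the scale.

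- Analysis 2, effect size 0.4, 90% power, 2.5% two-sided: n per arm = 2 × (2.241 + 1.282)² / 0.4² = 155.1, so 156. The article gives 157, which has 90.1% power by the noncentral t distribution. This agrees.
- Attrition: 375 / 0.75 = 500. This agrees.
- The 61 CAU women are used below only as the planned analysed number. At effect size 0.4 and two-sided 2.5%, 61 against 314 gives about 73% power rather than 90%, which is a separate matter.

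**Who is exposed to the rule.** Randomisation gives 5:5:2. Intervention arms: 500 × 10/12 ≈ 417. CAU: 500 × 2/12 ≈ 83.

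**Shift in the intervention mean.** Let f be the share of intervention women removed, and k the number of SDs by which their mean would have been worse than the mean of all women in those arms. The women who remain then have a mean better by

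shift = f × k / (1 − f).

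The article gives neither f nor k. Assumed ranges: f = 1-3% (about 4 to 12 of 417 women) and k = 0.5-1.5 SD.

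**Standard error for analysis 1**, in SD units and without baseline adjustment: √(1/314 + 1/61) = 0.140.

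| f | k | Shift (SD) | Share of 0.4 | Type I error (nominal 0.025, two-sided) |
|---|---|---|---|---|
| 1% | 0.5 | 0.01 × 0.5 / 0.99 = 0.005 | 1.3% | 0.0251 |
| 1% | 1.5 | 0.01 × 1.5 / 0.99 = 0.015 | 3.8% | 0.0259 |
| 2% | 1.0 | 0.02 × 1.0 / 0.98 = 0.020 | 5.1% | 0.0265 |
| 3% | 0.5 | 0.03 × 0.5 / 0.97 = 0.015 | 3.9% | 0.0259 |
| 3% | 1.5 | 0.03 × 1.5 / 0.97 = 0.046 | 11.6% | 0.0331 |

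The shift is between 0.005 / 0.140 ≈ 4% and 0.046 / 0.140 ≈ 33% of one standard error. At an extreme of 5% removed and 2 SD worse, it is 0.05 × 2 / 0.95 = 0.105 SD with type I error 0.070. Nothing in the article suggests removals on that scale.

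**Direction.** If k is positive, the shift favours the interventions in analysis 1 and in either arm against CAU. In ETPB against MB both arms are exposed, so no direction is fixed.

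**The case against.** The strongest reply is that the rule protects staff. Questionnaires are completed with trained researchers, and follow-up is a visit with video-recording, so a woman who has harmed someone may be a risk to the next person who meets her. No remote mode for HADS+I is described, and using one only for these women would add a mode difference confined to the intervention arms. This stands as a reason to leave the mode of contact to the investigators. It does not justify ending data collection in every case: Process evaluation already includes telephone interviews with mothers.

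A second reply is that the intention-to-treat definition is not literally contradicted. These women remain randomised participants with missing outcomes, and Planned analysis covers discontinuation and missing values. That is right as far as it goes. The fault is that the trial itself creates the missing outcomes, in one part of the comparison only.

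A third reply concerns size. Some intervention women will attend no session, and some removed women might have fallen within the 25% attrition anyway. Both points keep the likely number low.

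A reader might infer more than the documents support:

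- That the rule always flatters the interventions, or removes the worst outcomes. Harm is not defined, HADS+I is self-reported with 14 of its 18 items on anxiety and depression, and no section says these women would score worse.
- That harm goes unrecorded. Facilitators still report concerns to the project manager, and SAE reporting under Safety reporting and Recording and reporting of adverse events does not depend on outcome follow-up. What is lost is these women's follow-up scores, including for the check on worsening distress described under Data Monitoring Committee.
- That routine-data linkage stops for them. The article does not say so.

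**Conclusion.** The point holds as a minor but avoidable design fault. The rule imposes outcome loss after randomisation on one side of analysis 1, and of each intervention against CAU. It is inconsistent with keeping other intervention leavers in follow-up and with the aim of analysing everyone randomised.

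That it would favour the interventions is a plausible inference from the irritability items, not a stated fact. Under the assumed 1-3% removed and 0.5-1.5 SD worse, the shift is about 0.005-0.046 SD, or 1-12% of the 0.4 design effect, with type I error of 0.0251-0.0331 against 0.025. Both ranges are assumptions. The bias is probably small, and the case for change rests mainly on how little the change costs.

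**What to change.** 1. In Potential harms, delete the second half of the sentence, the part that ends data collection. Leave attendance at the groups as the sponsor decides.
2. Keep these women in follow-up unless they withdraw consent. Leave the mode of contact to the investigators' safety judgement; remote collection of HADS+I is one example.
3. Report the number removed by arm.
4. Where no score is obtained, add a delta-adjusted sensitivity analysis in which these women's imputed HADS+I is made worse than predicted by a stated range, for instance the 0.5-1.5 SD assumed here.

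The cost is one clause, a few questionnaires collected in a different mode, and one extra sensitivity analysis. The video outcome will usually still be missing for these women. Recruitment ended in March 2018 according to Trial status. Where follow-up is already complete, items 3 and 4 remain possible.

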#### Safety reporting

The research team will ask permission from participants to notify their General Practitioner (GP) and/or other relevant health and social care workers of her participation in the research. All participants will be told during the consent process that if a significant risk of harm to themselves or their baby/child(ren) is identified, the research team will notify their GP and/or other relevant health and social care professional(s). As previously discussed, structures are in place for group practitioners and researchers to follow should incidents occur relating to the safety of participants and/or their children. When there is a health risk or medical emergency, procedures will be followed including alerting emergency services, GPs or social work services as appropriate. Incidents of this nature, or serious adverse events (SAEs), will always be reported to the PM who will inform the CI.

#### Recording and reporting of adverse events

Any SAE (Table 1) occurring to a research participant will be reported to the NHS West of Scotland Research Ethics Committee (REC), which gave a favourable opinion on the study, when in the opinion of the CI the event was:
Related - that is it resulted from administration of any research procedures, andUnexpected - that is the type of event is not an expected occurrence.

**Table 1 Tab1:** Definition of serious adverse events

Any adverse event or adverse reaction that:	
a. Results in death	
b. Is life threatening	
c. Requires hospitalisation or prolongation of existing hospitalisation	
d. Results in persistent or significant disability or incapacity	
e. Consists of a congenital anomaly or birth defect	
f. Is otherwise considered medically significant by the investigator	
g. Is important but is not immediately life threatening or does not result in death or hospitalization, but may jeopardise the subject or may require intervention to prevent one of the other outcomes listed in the definitions above	

Reports of related and unexpected SAEs will be submitted to the REC within 15 days of the CI becoming aware of the event, using the report of SAE form for non-Clinical Trial of an Investigational Medicinal Product (non-CTIMPS) published on the National Research Ethics Service (NRES) website (https://www.hra.nhs.uk/approvals-amendments/managing-your-approval/safety-reporting/).

